## Abstract

**Background:**

Non-specific low back pain (NLBP) is a major global socioeconomic burden, and the prevalence of NLBP is still on the rise. At present, there is no ideal drug to cure this disease. This may be the reason why patients often use complementary therapies. Among them, extracorporeal shock wave therapy (ESWT) has gradually received more attention and has become the main treatment method for NLBP. The purpose of this study is to provide scientific evidence for the effect and safety of meridian theory-based ESWT on NLBP.

**Objective:**

This study aims to evaluate the effect and safety of meridian theory-based ESWT on NLBP. This study will also provide more high-quality experimental evidence for the clinical application of meridian theory-based ESWT for the treatment of NLBP in future.

**Methods:**

The study design is a single-blind, multi-center, randomized controlled trial. 66 patients with NLBP, aged 18 to 60 years, will be randomly divided into two groups: the experimental group (*N* = 33), which will receive meridian theory-based ESWT application, and the control group (*N* = 33) which will receive conventional ESWT treatment. These two applications will be carried out twice a week for two weeks. The primary outcome will be the Visual Analog Scale (VAS), and the secondary outcomes will be Oswestry Disability Index (ODI), Surface Electromyography (sEMG), and Patient Health Questionnaire-15 (PHQ-15). All outcomes will be evaluated at baseline and after the intervention (7 days, 14 days).

**Discussion:**

Results of this trial will contribute to providing rigorous clinical evidence for the efficacy and security of meridian theory-based ESWT for NLBP.

*Trial registration*: Chinese Clinical Trial Registry, ChiCTR2100051049. Registered on 10 September 2021, http://www.chictr.org.cn/showproj.aspx?proj=46316.

## Background

Low back pain is the major cause of dysfunction, affecting all age groups and being more common in adults [1, 2]. At the same time, the prevalence and burden of low back pain increase with age [3]. Many patients with low back pain cannot be specifically diagnosed, and approximately 85% of cases cannot be attributed to specific pathological changes or nerve root irritation [4]; therefore, most patients with low back pain have NLBP [5]. Pain and dysfunction are common features of NLBP [6, 7].

At present, most treatments for NLBP have limited efficacy and a high recurrence rate [8]. The main purpose of clinical treatment of NLBP is to relieve pain and improve the quality of life of patients. There are many clinical treatments for NLBP, including conservative therapy and surgery [9–11]. Conservative therapy including bed rest, drug therapy, physical exercise, and exercise therapy can relieve NLBP to a certain extent, but there are also many drawbacks; Surgical treatment is accompanied by problems such as postoperative infection and poor long-term efficacy, and the high cost brings a heavy economic burden to patients [12]. Therefore, there is an urgent need for a safe, effective, and economical treatment for NLBP.

ESWT has been extensively used for the treatment of NLBP in recent years [13, 14]. ESWT is a therapeutic method that applies shock waves to lesions from the inner body to boost blood flow and stimulate or reactivate affected connective tissue (including tendons and bones) to relieve pain and improve dysfunction [15]. Recently, based on the meridian theory of Traditional Chinese Medicine(TCM), ESWT combined with acupoint stimulation has played a therapeutic role [16]. The purpose of this study is to observe the clinical efficacy of meridian theory-based ESWT on pain and dysfunction in NLBP patients.

## Methods

### Study design

This is a single-blind, multi-center, randomized placebo-controlled trial supported by Henan Provincial Administration of TCM. The trial will be jointly conducted by three centers in Zhengzhou, China: the First Affiliated Hospital of Henan University of CM, Henan Provincial Hospital of CM, and the Third Affiliated Hospital of Henan University of CM. Patients between 18 and 60 years of age with NLBP will be included. When participants are eligible for inclusion after being informed about the purpose and procedures of the study, they will be asked to sign an informed consent form. Then, Sixty-six patients will be recruited and randomly assigned to two groups: the experimental group (*N* = 33) and the control group (*N* = 33). Participants in the experimental group will receive ESWT based on meridian theory and participants of the control group will receive conventional ESWT treatment. Patients will be treated twice a week for two weeks. All the participants will be assessed 3 times: baseline (evaluation before treatment), the middle of the treatment (7 days after treatment starts), and the end of the treatment (14 days after treatment starts). The volunteers will complete the VAS, ODI, sEMG, and PHQ-15 assessments. The study flowchart is shown in Fig. 1. The trial process chart is shown in Table 1.

**Fig. 1 Fig1:**
[figure not shown]
Flowchart of the trial

**Table 1 Tab1:** Timing of treatment assessments and data collection

Timepoint	Study period			
	Enrolment	Baseline	Treatment phase	
	− 1 week	0 week	1 week	2 weeks
Enrolment				
Eligibility screen	×			
Informed consent	×			
Medical history	×			
Merger disease	×			
Randomization		×		
Interventions				
Experimental group		×	×	×
Control group		×	×	×
Assessments				
VAS	×	×	×	×
ODI		×	×	×
sEMG		×	×	×
Safety evaluation		×	×	×
Adverse events		×	×	×

### Ethics committee approval

This trial was reviewed by the ethics committee of the First Affiliated Hospital of Henan University of CM on August 24, 2021 (reference number: 2021HL-203-01). Written informed consent will be obtained from all participants. The study was registered with the Chinese Clinical Trial Registry (Identifier ChiCTR2100051049.)

### Participants

The main participants will be recruited independently through the outpatient and inpatient systems of three hospitals in China—(the First Affiliated Hospital of Henan University of CM, Henan Provincial Hospital of CM, and the Third Affiliated Hospital of Henan University of CM). To recruit participants, three independent centers will publish individually online study advertisements through hospital websites and WeChat and we will also put up posters and distribute leaflets offline in crowded areas of the hospital. The recruitment of participants began on 15 September 2021 and is expected to end on 9 December 2022, or it may be completed earlier if a sufficient number of patients are recruited.

### Inclusion criteria

Participants meeting the following criteria will be included:Male or female patients aged 18–60;Low back pain that persists for more than three months without a specific cause;VAS score greater than 3 points;Patients with normal intelligence and language skills;NLBP patients who have not received any treatment in the past two weeks;Agree to receive only ESWT-related treatments during treatment;Willing to volunteer for the trial and provide informed consent.

### Exclusion criteria

Participants who report any of the following will be excluded:Patients will be excluded when low back pain is caused by specific pathological factors such as tumors, Osteoporosis, lumbar fractures, rheumatoid arthritis;The lower extremities are affected by neurological malfunction due to NLBP;Known or suspected serious congenital or acquired spinal pathology, lumbar disc herniation with nerve symptoms, spinal deformity, spondyloarthropathy, etc.;Patients with other serious diseases such as immune diseases, endocrine diseases, and abnormal liver and kidney functions;Patients deemed by researchers as ineligible to participate due to severely abnormal/unstable laboratory test results or vital signs;ESWT -phobic patients.

### Elimination criteria

Patients who do not meet the diagnostic criteria for NLBP and are erroneously included;Patients who are judged by the researchers as unsuitable to continue the trial because of serious adverse complications.

### Randomization

Participants who are eligible in the screening phase and agree to sign the consent form will be randomly assigned to the experimental group or the control group. The random sequence numbers will be generated through the computer. The allocation will be concealed using consecutively numbered sealed and opaque envelopes. For this, an independent researcher who will not participate in other study procedures will carry out the randomisation process to avoid bias. The allocation sequence will be generated by a specialized statistician who does not participate in this experiment. Relevant independent researchers in three centres will recruit participants and assign them to two different intervention groups.

### Blinding

This is a single-blind study. All other researchers, such as assessors and data analysts, will be unaware of group assignments. To confirm whether participants achieved blinding, assessors will use a "blinding test" questionnaire to ask participants what type of treatment they think they received after the first and final treatment.

### Sample size calculation

We will conduct this study in a randomized controlled trial design method and the main observed outcome was the improvement of patients’ pain. Previously, we conducted a small sample(12 cases) of clinical observation and found that the 1-week experimental group received ESWT with meridian theory-based and the control group received conventional ESWT treatment can reduce the level of the VAS scale by 3.45 ± 1.31 and 2.33 ± 1.13, respectively. The significance test level was 0.05, and the test power was 0.9. The sample size was calculated by using:$$N = 2 \times \left[ {\left( {z_{\alpha } + z_{\beta } } \right) \times \sigma /\delta } \right]^{2}$$

*N* is the required sample size for each group, and the sample size of each group is equal. Where *α* is 0.05 and *β* is 0.1, the normal distribution quantile table shows that:$$Z_{{\alpha /{2}}} = {1}.{96},\;{\text{and}}\;Z_{\beta } = {1}.{282}.$$

*σ* and *δ* represent the population standard deviation and allowable error, which are 1.31 and 1.12, respectively. By substituting the above data into the formula, 29 cases will be needed in each group. Taking into account the 10% expulsion rate, a total sample of 66 participants will be sufficient.

### Interventions

The intervention treatment period will include 4 sessions during 2 weeks. Licensed medical doctors who are bothering at least 4 years of clinical experience will perform the intervention, and we will conduct standardized training for the clinicians who implement the treatment in the three research centers before the treatment and try to maintain the consistency of the research. Meanwhile, each patient will receive the same routine therapeutic drug and rehabilitation. The interventions for the two groups are as follows:

**Routine therapeutic drug treatment:** All patients will use blood pressure control, blood lipid adjustment, blood sugar control, and nutritional nerve drug as routine therapeutic drug treatment following the physicians' instructions.

**Extracorporeal shock wave intervention:** ESWT will be applied by a BTL-5000 pneumatic ballistic ESWT machine, 8.0–10 Hz, 1.6–3.0 bar energy density, 2000 pulses, twice a week for two weeks.

**The experimental group:** In addition to the routine treatment for patients with low back pain, ESWT will also be performed at Huantiao(GB30), Baihuanshu(BL30), Xiaochangshu(BL27), Pangguangshu(BL28), Guanyuanshu(BL26), Qihaishu(BL24), Dachangshu(BL25), Sanjiaoshu(BL22), Chengfu(BL36), Yaoyan(EX-B7) and Yaoyi (EX-B6) in the experimental group [17] (Table 2).

**Table 2 Tab2:** Locations of acupoints for ESWT

Acupoints	Location
Huantiao (GB30)	In the buttocks region, at the junction of the lateral one-third and medial two-thirds of the line connecting the prominence of the greater trochanter with the sacral hiatus
Baihuanshu (BL30)	In the sacral region, at the same level as the fourth posterior sacral foramen, 1.5 B-cun lateral to the median sacral crest
Xiaochangshu (BL27)	In the sacral region, at the same level as the first posterior sacral foramen, and 1.5 B-cun lateral to the median sacral crest
Pangguangshu (BL28)	In the sacral region, at the same level as the second posterior sacral foramen, and 1.5 B-cun lateral to the median sacral crest
Guanyuanshu (BL26)	In the lumbar region, at the same level as the inferior border of the spinous process of the fifth lumbar vertebra (L5), 1.5 B-cun lateral to the posterior median line
Qihaishu (BL24)	In the lumbar region, at the same level as the inferior border of the spinous process of the third lumbar vertebra (L3), 1.5 B-cun lateral to the posterior median line
Dachangshu (BL25)	In the lumbar region, at the same level as the inferior border of the spinous process of the fourth lumbar vertebra (L4), 1.5 B-cun lateral to the posterior median line
Sanjiaoshu (BL22)	In the lumbar region, at the same level as the inferior border of the spinous process of the first lumbar vertebra (L1), 1.5 B-cun lateral to the posterior median line
Chengfu (BL36)	In the buttock region, at the midpoint of the gluteal fold
Yaoyan (EX-B7)	In the lumbar region, au niveau du rebord inferieur du processus epineux L4, lateral a la ligne mediane posterieurede 3, 5 cun
Yaoyi (EX-B6)	In the lumbar region, au niveau du rebord inferieur du processus epineux L4, lateral a la ligne mediane posterieurede 3 cun

**The control group:** The patient will be placed in the prone position to expose below the seventh rib and above the gluteal groove. The clinician will use the thumbs of both hands to press and palpate from the middle to the sides with the strength that the patient can bear, and then the doctor will mark the pressure pain points with a marker according to the shape of the muscle. ESWT will then be performed at the tender point of the control group.

### Outcome measures

#### Primary outcome

**Visual Analog Scale (VAS):** Pain intensity will be assessed using VAS [18]. This questionnaire has good reliability and validity,and has the advantages of simplicity, time-saving, convenient operation, and wide application to a wide range of people. On the paper was drawn a horizontal line 10 cm long. One end of the horizontal line indicated no pain, the other end indicated severe pain; the middle part indicated different degrees of pain. On the horizontal line, we let the patient mark the degree of pain based on the feeling of self. Many clinical trials for NLBP use VAS as their main outcome.

#### Secondary outcome

**Oswestry Disability Index (ODI):** The ODI will be a simple and comprehensive patient-rated outcome used to assess Lumbar spine dysfunction [19]. The ODI is used to measure NLBP-related dysfunction and it includes 10 questions about daily activities, including pain intensity, personal care, lifting, walking, sitting, standing, sleeping, sexual life, social life and traveling. The ODI has six response categories. Each item scores from 0 (better) to 5 (worst). Each score will be transferred into a 0 to 100 scale, with lower scores indicating lesser Lumbar spine dysfunction.

**Surface electromyography (sEMG):** The sEMG [20] evaluation is an objective method to obtain the electromyographic signal during muscle activity, which is achieved by placing surface electrodes on the muscle layer. It can perform a quantitative and qualitative analysis of the function of muscles and can study multiple muscles in the body at the same time. It has the advantages of innovativeness, safety and reliability, convenient operation, and objective quantification.

**Patient Health Questionnaire-15 (PHQ-15):** An assessment of somatization and thus the severity of its symptoms in clinical practice and research can be done using the PHQ-15, a brief, self-administered questionnaire [21]. Among 15 somatic symptoms in the PHQ-1 5, each symptom is scored from 0 to 2 ("not bothered at all" to "bothered a lot"). Results included functional status as assessed by the 20-item Short-Form General Health Survey (SF-20), self-reported sick days, and clinic visits, as well as symptom-related difficulty. All six subscales of SF-20 decremented stepwise as PHQ-15 somatic symptoms severity increased.

### Data management

Case report forms(CRFs) will record all information about participants truthfully, completely, accurately and promptly.All relevant information of participants will be kept strictly confidential. After the trial, the quality control team will strictly review the submitted CRFs and ensure their accuracy and completeness of the CRFs.

### Statistical analysis

We will intend to apply SPSS V.20 software to the statistical analysis of all results. The CI will be established at 95%, and the significance level at 0.05. Missing data refers to the use of actual observations without imputation when the dropout rate does not exceed 10%. The normality test will be applied to all data first. Then, mean ± SD will be used to describe the data that fit the normal distribution; medians and interquartile ranges will be used to represent central and discrete trends in quantitative data that do not fit the normal distribution. The t-test and analysis of variance(ANOVA) will be applied to quantitative data, and the rank-sum test will be applied to count data to compare differences between groups. Sensitivity analysis will be carried out if necessary. *P* < 0.05 will be considered statistically significant.

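### The primary VAS comparison names no baseline covariate although baseline VAS is measured; the test is valid, but a baseline-adjusted analysis would be more precise and would remove chance baseline imbalance

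*Protocol article*

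**What the plan says.** The Statistical analysis section of the protocol article gives one rule for quantitative outcomes: "The t-test and analysis of variance(ANOVA) will be applied to quantitative data". Its stated purpose is to compare the groups. The primary outcome falls under this rule, since "Pain intensity will be assessed using VAS" on a 10 cm line. The section names no covariate, and it does not say whether the final VAS or the change in VAS is tested, or at which visit.

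Baseline values are planned. The Study design section says "All the participants will be assessed 3 times: baseline (evaluation before treatment", with later assessments at 7 and 14 days. The abstract agrees: "All outcomes will be evaluated at baseline and after the intervention (7 days, 14 days". Table 1 marks VAS at enrolment, week 0, week 1 and week 2.

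The Sample size calculation works on the reduction in VAS (3.45 ± 1.31 versus 2.33 ± 1.13), and "The significance test level was 0.05, and the test power was 0.9". The Randomization section says only that "The random sequence numbers will be generated through the computer"; it describes no stratification by baseline pain.

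**The concern.** With about 29 evaluable patients per arm and no stratification on pain, the arms can differ by chance in baseline VAS. Baseline pain usually predicts later pain, so part of that difference passes into the result. A t-test on final VAS carries it forward in the same direction. A t-test on change over-corrects, because patients who start high tend to fall further for reasons unrelated to treatment. ANCOVA on the baseline value estimates the right amount of correction from the data and also lowers the residual variance.

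At stake are the width of the confidence interval for the primary comparison and how far a single trial's estimate is moved by the luck of allocation. The gain would also give some margin if the true difference is below 1.12, a figure taken from a 12-case observation.

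**Working it through.** **Inputs from the protocol article (Sample size calculation):** difference δ = 1.12; SD σ = 1.31, the SD of the reduction in VAS in the experimental group of the earlier observation; normal quantiles 1.96 and 1.282, so the test is two-sided at 0.05 with power 0.90; equal groups; 10% loss.

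**Assumptions:** the correlation ρ between baseline and follow-up VAS is not given, so 0.3, 0.5 and 0.7 are used. VAS is taken to have the same SD at both times. The change SD of 1.31, observed at one week, is applied to day 14.

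**Step 1: the plan's own figure.** n per group = 2 × [(1.96 + 1.282) × 1.31 / 1.12]² = 28.76, rounded up to 29. Allowing for loss, 29 / 0.9 = 32.2, rounded up to 33 per group and 66 in total. Both stated figures reproduce. At 29 per group the power is 0.902 by the normal approximation and 0.892 by the noncentral t distribution. The t-based figure is used below.

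**Step 2: the SDs implied at each correlation.**
- Raw VAS: σ_raw = 1.31 / √[2(1 − ρ)].
- ANCOVA residual: σ_raw × √(1 − ρ²), which equals 1.31 × √[(1 + ρ)/2].
- Variance ratio, ANCOVA to change score: (1 + ρ)/2.
- Variance ratio, ANCOVA to raw final score: 1 − ρ².

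**Step 3: results at 29 per arm and a difference of 1.12.**

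| Assumed ρ | 0.3 | 0.5 | 0.7 |
|---|---|---|---|
| Raw VAS SD | 1.11 | 1.31 | 1.69 |
| ANCOVA residual SD | 1.06 | 1.13 | 1.21 |
| Variance ratio, ANCOVA / change | 0.65 | 0.75 | 0.85 |
| Variance ratio, ANCOVA / raw final | 0.91 | 0.75 | 0.51 |
| Power, t-test on change | 0.89 | 0.89 | 0.89 |
| Power, t-test on raw day-14 VAS | 0.97 | 0.89 | 0.70 |
| Power, ANCOVA | 0.98 | 0.96 | 0.93 |

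A simulation of 4,000 trials at each correlation agreed with these powers to within about half a percentage point. The mean estimate of all three methods lay within 0.01 of the true difference, so none is biased over repeated randomisation.

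**Step 4: a chance baseline difference of one standard error.** The standard error of the baseline difference is σ_raw × √(2/29), or 0.29 / 0.34 / 0.44 cm at the three correlations.
- The raw final-score estimate moves by ρ times this: 0.09 / 0.17 / 0.31 cm, in the direction of the imbalance.
- The change-score estimate moves by (1 − ρ) times this: 0.20 / 0.17 / 0.13 cm, in the opposite direction.
- ANCOVA removes this shift.

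These shifts compare with a planned difference of 1.12 cm.

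**The case against.** The strongest reply is that the named test is sound and the trial is sized for it. That stands: Step 1 reproduces the sample size, and randomisation keeps the unadjusted comparison unbiased.

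It can also be said that baseline is not ignored. The Sample size calculation describes the main outcome as improvement in pain and uses reductions in VAS, so change may well be what is tested. That also stands in part. Baseline then enters by subtraction, and what is left is regression to the mean and the loss against ANCOVA shown in Step 3.

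Three stronger readings are tempting, but the article does not support them.

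- **An inflated false-positive rate.** A reader might infer that days 7 and 14 are entered in the ANOVA as independent observations. The Statistical analysis section does not say so. With three assessments, the term may mean a repeated-measures ANOVA.
- **A mismatch between the SD used for sizing and the SD of the analysis.** This arises only if raw VAS is tested, which is not stated. Even then the two SDs coincide at ρ = 0.5, and the raw test does better than the change-score test at 0.3. It falls clearly short only at higher correlations.
- **Precision lost by leaving out centre.** The Study design section says "The trial will be jointly conducted by three centers in Zhengzhou, China", but the article gives no between-centre variance and describes no stratification by centre. No gain can be calculated, and no stratification factor is being ignored.

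**Conclusion.** The point holds as one of efficiency and of protection against chance imbalance. It is not one of validity. The article names the t-test and ANOVA without a baseline covariate for an outcome that is measured at baseline, and a more precise analysis of the same data is available.

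Against a t-test on change, adjustment cuts the variance by 35% / 25% / 15% at assumed correlations of 0.3 / 0.5 / 0.7 and raises power from about 0.89 to 0.98 / 0.96 / 0.93. Against a t-test on raw day-14 VAS, the gain is negligible at 0.3 (0.97 to 0.98) and large at 0.7 (0.70 to 0.93). ANCOVA has the highest power at each correlation examined.

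The sizes rest on the assumed correlation, on equal variances at baseline and follow-up, and on the one-week change SD holding at day 14. The entry rule of a VAS above 3 may lower the correlation by narrowing the baseline range. A reader might conclude that the planned analysis is biased or the trial underpowered as designed; neither follows.

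**What to change.** In the Statistical analysis section, name the primary analysis as an ANCOVA of day-14 VAS on treatment group, with week-0 VAS as covariate, and report the adjusted difference with its 95% CI. State that the week-0 value is the baseline, because Table 1 also marks VAS at enrolment.

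A repeated-measures model over days 7 and 14 with baseline VAS as covariate is an acceptable alternative. A centre term is optional. Use the same baseline adjustment for each secondary quantitative outcome that has a baseline value.

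The cost is a change of wording, made before any unblinded look at the data. The 66 patients, the visits and the measurements of VAS stay as they are.

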### Safety evaluation and adverse events

The whole trial will monitor and report all adverse events (AEs). Any uncomfortable symptoms or disease during this study will be recognized as adverse events, such as localized hematoma, allergies, pain, dizziness, vomiting, or palpitations. The study will detail record AEs—including symptoms, onset, and end date, severity, relationship with ESWT, and outcome. Participants will stop treating if the treatments cause serious aggravation of symptoms and undergo related tests and treatments. Researchers will immediately report SAEs (e.g., requiring hospitalization, causing disability, or impaired ability to work) to the ethics committee of the First Affiliated Hospital of Henan University of CM and suspend the study.

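### The rank-sum test is assigned to count data and t-test/ANOVA to all quantitative data, so the non-parametric test sits with the wrong data type (minor to moderate wording error)

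*Protocol article*

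**What the plan says.** The Statistical analysis section of the protocol article sets out three steps.

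- Screening: "The normality test will be applied to all data first".
- Description: mean ± SD where normality holds; otherwise "medians and interquartile ranges will be used to represent central and discrete trends in quantitative data that do not fit the normal distribution".
- Comparison of measurements, with no condition on normality: "The t-test and analysis of variance(ANOVA) will be applied to quantitative data".
- Comparison of everything else, in the second half of that sentence: "the rank-sum test will be applied to count data to compare differences between groups".

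The normality result therefore changes how data are described but not how they are compared. The article names no chi-square, exact or other categorical test.

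The data to which these rules could apply are as follows.

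- VAS, ODI, sEMG and PHQ-15 are all measurements or scores. For the VAS, "On the paper was drawn a horizontal line 10 cm long".
- Adverse events are recorded in detail, "including symptoms, onset, and end date, severity, relationship with ESWT, and outcome" (Safety evaluation and adverse events).
- The Blinding section has a questionnaire "to ask participants what type of treatment they think they received after the first and final treatment".
- There are three recruiting centres (Study design).

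**The concern.** Set against quantitative data, count data reads most naturally as categorical data. A rank-sum test needs values with an order. Centre, type of adverse event and perceived treatment have no inherent order, so ranking them means numbering the categories arbitrarily, and the p-value then depends on that choice.

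The second fault is internal. The section sends non-normal measurements to medians and interquartile ranges, then compares all measurements by means. The rank-sum test that would match those medians is named one clause later, for another kind of data. The two halves of the comparison sentence look crossed.

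An analyst who follows the text can produce an uninterpretable comparison of unordered items and, for skewed outcomes, a test that does not match the summary beside it. An analyst who departs from the text makes an unplanned choice of test.

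**Working it through.** **1. The plan's own figure.** The Sample size calculation section uses SD 1.31, difference 1.12, z-values 1.96 and 1.282: "The significance test level was 0.05, and the test power was 0.9".

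N = 2 × [(1.96 + 1.282) × 1.31 / 1.12]² = 28.76, rounded up to 29 per group. With 10% loss, 29 / 0.9 = 32.2, so 33 per group and 66 in total. The figure reproduces, and nothing below changes it.

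**2. Unordered item with three categories.** The article gives neither the answer options of the blinding questionnaire nor any data. Assume three options (experimental / control / don't know) and illustrative counts of 15/3/15 and 6/21/6, with 33 per arm.

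- *Chi-square.* Expected counts are 10.5, 12 and 10.5 in each arm. The statistic is 4 × (4.5²/10.5) + 2 × (9²/12) = 7.71 + 13.50 = 21.21 on 2 df, p = 0.00002.
- *Rank-sum, coded experimental 1, control 2, don't know 3.* Mid-ranks are 11, 33.5 and 56. The first arm's rank sum is 15 × 11 + 3 × 33.5 + 15 × 56 = 1105.5. Its null expectation is 33 × 67 / 2 = 1105.5, so z = 0 and p = 1.00.
- *Rank-sum, coded control 1, experimental 2, don't know 3.* Mid-ranks are 12.5, 35 and 56. The rank sum is 3 × 12.5 + 15 × 35 + 15 × 56 = 1402.5. The tie-corrected variance is (33 × 33 / 12) × [67 − (13,800 + 2 × 9,240) / (66 × 65)] = 5,397, SD 73.5. Then z = 297 / 73.5 = 4.04 and p = 0.00005.

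The same data give opposite answers under two numberings.

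**3. Two categories.** On a 2×2 table the tie-corrected rank-sum statistic equals the uncorrected chi-square times (N − 1)/N. Example: 5/33 versus 12/33 gives chi-square 3.882, p = 0.0488. Multiplied by 65/66 it is 3.824, p = 0.0505, which is the rank-sum p-value. Exact enumeration at 33 per arm puts the rank-sum type I error between 0.004 and 0.056 for true event rates from 2% to 20%.

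**4. Skewed measurements.** Simulation with 33 per arm, 8,000 replicates, assumed shapes, and a shift of 0.6 SD for power:

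| Shape | t-test type I error | t-test power | Rank-sum power |
|---|---|---|---|
| Normal | 0.047 | 0.67 | 0.65 |
| Lognormal, sigma 0.5 | 0.044 | 0.69 | 0.83 |
| Exponential | 0.046 | 0.68 | 0.91 |
| Lognormal, sigma 1 | 0.045 | 0.74 | 0.99 |

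The t-test is not anti-conservative under any of these shapes. What it loses under skew is power.

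**The case against.** **No listed outcome is an unordered category.** This is right. All four efficacy outcomes are scores or measurements, so the count-data clause reaches only centre, type of adverse event, the blinding check and similar items. None of these decides the trial.

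**The three-option example is assumed.** This is also right. With two answer options, rank-sum is almost chi-square. With don't know coded between the two treatments, the same counts give 0.00005, close to chi-square. The example shows dependence on coding, not how this questionnaire will behave. Centre and type of adverse event have no natural middle category, however, so the weakness does not rest on the questionnaire alone.

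**Count data might mean numbers of events per participant.** Rank-sum would then be defensible. The contrast with quantitative data makes this the less natural reading, and the mismatch between medians and t-test would remain.

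**Categorical tests may be left to a fuller plan.** A missing chi-square sentence would be no finding. Here the article positively names a test for these data.

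**Letting a normality test choose the comparison is itself contested.** That is fair, and a t-test at this size is defensible. The point is only that the section reports medians and then tests means.

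**A stronger reading to avoid.** A reader might infer that adverse-event incidence gets p-values that are too small, because with 33 per arm rank-sum gives 0.041, 0.021 and 0.047 for 4 versus 0, 5 versus 0 and 6 versus 1, where Fisher's test gives 0.114, 0.053 and 0.105. That does not follow. The type I error in step 3 of the working never exceeds 0.056 on the grid examined and is well below 0.05 for event rates of 5% or less. Barnard's unconditional exact test gives 0.040, 0.019 and 0.057 for the same tables; Boschloo's gives 0.070, 0.036 and 0.064. The gap mostly reflects Fisher's conservatism.

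**Conclusion.** The concern holds as a misassigned rule of minor to moderate weight. The article attaches the rank-sum test to categorical data and leaves non-normal measurements with tests of means, against its own descriptive rule.

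- Unordered items with three or more categories: the rank-sum p-value is arbitrary (1.00 or 0.00005 in the illustration). This rests on reading count data as categorical and, for the blinding questionnaire, on an assumed don't-know option.
- Two-category items: no material error.
- Clearly skewed measurements: type I error is held. Power may fall, for example 0.69 against 0.83 or 0.68 against 0.91 under assumed shapes, and the test does not match the median.

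It would be tempting to conclude that the primary analysis is invalid. The documents do not support that: VAS is a measurement, a t-test is acceptable for it at about 33 per arm, and the sample size of 66 is unaffected.

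**What to change.** Replace the comparison sentence in the Statistical analysis section with:

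> Categorical data will be compared by chi-square test, or by an exact test when expected counts are small; ordinal data and clearly non-normal quantitative data by rank-sum test; other quantitative data by t-test/ANOVA.

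If the intention is to keep the t-test for VAS whatever its shape, say so and report means alongside it. That would also remove the inconsistency for the primary outcome.

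The cost is one sentence, settled before the analysis. Recruitment, data collection and the total of 66 do not change.
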